## Abstract

**Background:**

Evidence demonstrates that physical exercise and psychological wellbeing are closely interlinked, particularly in older-aged women. However, research investigating how different forms of exercise influence mental health in older-aged women is underdeveloped.

**Methods/Design:**

A randomized controlled trial (N = 300) will assess the relative effectiveness of two different exercise programs (whole-body vibration and Multicomponent Training) for improving psychological wellbeing in older-aged women. The following outcomes will be assessed at three time points (that is, pre, post, and follow-up): psychological wellbeing, proactive attitude, quality of life, and happiness.

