### Interventions

The interventions protocol will consist of six months of training for both groups of vibratory platform and Multicomponent Training. Both groups, WBV and Multicomponent Training, will follow three training sessions per week, with a recovery time between sessions ranging from 24 to 72 hours.

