### WBV training

After the warm-up consisting in eight minutes of static cycling, active stretching and joint mobility, participants will perform the WBV training. The vibration stimulus will consist of uniform vertical oscillations Power Plate® Next Generation (Power Plate North America, Northbrook, IL, USA). Subjects will stand on the platform holding quarter squat positions with the feet shoulder-width apart. Then, they will perform ankle extensions with the following work sequence (establishing a rhythm of 100 bpm: 1 bpm for the concentric phase; and 5 bpm for the eccentric phase). After the familiarization 2-weeks, subjects will train 3 days per week for 6 months (72 sessions) using a vibrating training program that will begin with 5 sets and a frequency of 35 Hz per session and increasing by 11 sets and 40 Hz frequency for the last month, maintaining a series of parameters: vibration amplitude (4 mm) working time (60 seconds) and recovery time (60 seconds).

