### Multicomponent Training

In the same way, and after the warm-up consisting in eight minutes of static cycling, active stretching and joint mobility, participants will perform the Multicomponent Training. This training will combine vertical jumps and high-intensity walking. During the first month, small reactive vertical jumps (without knee and ankle flexion) will be performed. After the first month, subjects will perform drop jumps progressively starting at a height of 5 cm and finishing at 25 cm at the end of the program (increases of 5 cm each month). Additionally, the sets will be increased from 4×10 jumps to 6×10 each week, finishing the last week with 4×10. In this sense, the drop jumps will be the same each month but the total load (imposed by height) will increase progressively. Regarding the aerobic exercise, the load will increase progressively along the six months. The intensity will range between 50 to 75% of reserve heart rate; the volume will range between 30 to 60 minutes.

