### Control group

Control group participants will be asked to continue their daily lives normally and maintain regular physical activity during the six-month duration of the study.

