### Measurements

Besides the psychological screening baseline at one week after the beginning of training (T1), all participants will be assessed at three months (T2) and six months (T3).Moreover, at the baseline assessment, questions on demographic variables (for example, age, marital status, work, educational level, socioeconomic status), psychiatric history (for example, previous diagnosis of depression and/or anxiety, family history regarding psychiatric diagnosis), and/or health behaviors (for example, alcohol use, smoking habits, physical activity) will be included.

All participating sample were screened for psychological aspects by the following standardized measures:

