## Planned statistical analyses

The demographic and clinical characteristics of the three study groups will be compared at baseline to verify their homogeneity. To do this, analysis of variance (ANOVA) for continuous variables and chi-square test of Mantel-Haenszel test for discrete variables will be used. Complete and intent-to-treat analysis will be accomplished to compare primary outcome treatments. First, prevalence of happiness, proactive attitude, psychological wellbeing and quality of life will be displayed infrequency tables and both conditions (control and intervention)will be compared using the chi-square (Fisher’s exact test when appropriate) and Student’ s *t*-test, for discrete and continues variables respectively. The effect of the intervention will be determined using multilevel analyses (mixed effect regression models) to compare baseline and follow-up measures of all continuous data. In all these analyses a *P*-value of <0.05 will be considered statistically significant.

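### The abstract's pre, post and follow-up labels do not fit the visit schedule: T1 is dated after training starts, T2 is mid-training, T3 is end of training, and no visit follows training

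*Protocol article*

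**What the plan says.** The abstract (Methods/Design) announces assessments "at three time points (that is, pre, post, and follow-up". The Measurements section is the only place where visits are dated. It speaks of a "psychological screening baseline at one week after the beginning of training (T1", and then says "all participants will be assessed at three months (T2) and six months (T3". It names no later visit.

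Four statements bear on how long training and the study last:

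- Interventions: "The interventions protocol will consist of six months of training for both groups".
- WBV training: "After the familiarization 2-weeks, subjects will train 3 days per week for 6 months (72 sessions".
- Multicomponent Training, on the aerobic part: "the load will increase progressively along the six months".
- Control group: women are to "maintain regular physical activity during the six-month duration of the study".

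The Sample size calculation section makes the change in PGWBI and SF-12 scores primary. The Planned statistical analyses section uses mixed models "to compare baseline and follow-up measures of all continuous data", without saying which visits that covers.

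**The concern.** The abstract's three labels describe a design with a measurement before treatment, one after it, and one later still. The dated schedule describes another design: one visit just after training starts, one half-way through and one at its end. Both have three visits, so a reader is likely to match them in order and take T2 as *post* and T3 as *follow-up*. A score from half-way through the programme would then be presented as the result of the completed programme, and an end-of-training score as an assessment made some time after it.

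The first label also matters. The primary outcomes are changes in score, so the reference value enters every primary comparison. If T1 really is taken a week into training, any early response to starting exercise is already in the reference value and drops out of the measured change. By then each woman also knows her arm, which can affect self-reported wellbeing.

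**Working it through.** No sample-size or power figure is involved. The check compares visit dates with training dates.

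**Inputs**
- T1 at week 1 of training, T2 at 3 months, T3 at 6 months (Measurements).
- Training of 6 months in both exercise arms, three sessions per week (Interventions).
- WBV: 2 weeks of familiarization, then 72 sessions at 3 per week, also described as 6 months (WBV training).
- Study duration of 6 months (Control group).

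**Conversions**
- One month = 365.25 / 7 / 12 = 4.35 weeks.
- 3 months = 13.0 weeks; 6 months = 26.1 weeks.
- 72 sessions / 3 per week = 24 weeks.
- With familiarization: 2 + 24 = 26 weeks.
- Familiarization followed by six full calendar months: 2 + 26.1 = 28.1 weeks.

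**Where T3 falls relative to the last WBV session** (T3 minus end of training, in weeks)

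| Reading of the WBV programme | Training ends, week | T3 counted from first session (week 26.1) | T3 counted from T1 (week 27.1) |
|---|---|---|---|
| 24 weeks, no added familiarization time | 24 | +2.1 | +3.1 |
| 2 + 24 weeks | 26 | +0.1 | +1.1 |
| 2 weeks + six calendar months | 28.1 | −2.0 | −1.0 |

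T3 always lies between 2 weeks before and about 3 weeks after the last session. It is an end-of-training assessment on all six readings.

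**Where T2 falls.** Counted from the first session at three sessions per week, 13 × 3 = 39 sessions are done if there is no run-in, and (13 − 2) × 3 = 33 if the 2 weeks come first. That is 33/72 = 46% to 39/72 = 54% of the WBV programme. T2 is mid-training.

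**Where T1 falls.** One week at three sessions per week is about 3 sessions. In the WBV arm this could be a week of familiarization instead, because the text does not say which of the two begins training. Either way T1 is not before training.

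**Labels against schedule**

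| Abstract | Schedule as written |
|---|---|
| pre | not met: T1 is one week into training |
| post | T3 (end of training) |
| follow-up | no visit |
| no label | T2 (mid-training) |

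**Could T2 and T3 be counted from the end of training?** The Measurements section does not state their origin. On that count the visits would fall at months 6 + 3 = 9 and 6 + 6 = 12. That contradicts the six-month study in the Control group section and leaves no assessment at the end of training. It rescues *follow-up* only by breaking other statements.

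**The case against.** The strongest reply is that this is loose wording in an abstract. The Measurements section dates the visits in months, so a careful reader cannot mistake T2 for the end of training. The analysis section uses *follow-up* in the ordinary sense of any measurement after baseline. No section makes T2 the time point of the treatment effect. Ending assessment at six months is a legitimate design. All of this stands, and it limits the consequence. It does not remove the contradiction: the abstract states a design property that the schedule lacks, and the analysis section does not say which visit carries the primary comparison.

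On T1, one can point out that the Hypotheses and design section describes psychological screening of eligible women when they are approached, so a measurement before training may exist. That section gives it no visit label, however, and the Measurements section attaches the baseline to T1.

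Two stronger readings are tempting, and the document supports neither:

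- A reader might infer that the trial claims a lasting effect it cannot show. It makes no such claim. The hypotheses and the Discussion speak only of promoting or improving wellbeing, so there is nothing to withdraw.
- A reader might infer that WBV women are measured at T3 with training still to do: 2 weeks × 3 = 6 sessions, or 6/72 = 8%. This needs two assumptions that the text does not state: that familiarization precedes six full calendar months, and that T3 is counted from the first familiarization session. With 2 + 24 = 26 weeks there is no offset.

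**Conclusion.** The point holds as an internal inconsistency. The abstract promises one post-training follow-up visit and the schedule contains none. T2 comes at about half the programme (46% to 54% of WBV sessions), T3 is at the end of training to within about 3 weeks, and *pre* fails as written because T1 is dated after training begins.

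This rests on taking the six-month study duration at face value and on counting T2 and T3 from the start of training or from T1. The conclusion does not depend on how the familiarization weeks are counted. The size of any bias from a T1 taken during training cannot be given, because the document has no figure for early change.

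The fault affects how each visit's result will be read. It does not undermine the randomized comparison of the arms at T3. It should be corrected, and it is not fatal.

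**What to change.** Reconcile the abstract with the Measurements, Interventions, WBV training and Control group sections:

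1. State that T1 is taken before the first training session. If it really is taken a week into training, stop calling it pre or baseline.
2. Label T2 mid-training and T3 end of training, in the abstract as well as in Measurements.
3. Make end of training the time point for the primary change in PGWBI and SF-12.
4. State the time origin of T3, so that it falls at the end of training in both exercise arms and at the matching calendar week in controls. This requires saying whether the familiarization weeks lie inside or before the six months; the sections must be brought into agreement on that.
5. Drop *follow-up* from the abstract unless a later visit is really planned. In the analysis section the word can stay if it is defined as T2 and T3.

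The cost is a few sentences and one visit anchor. No visit, participant or training session is added, and no claim in the article has to be given up.

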**Discussion:**

Results will have important implications for preventing psychological and physiological disease in older-aged women and for managing health-related costs for this population group.

**Trial registration:**

Number NCT01966562 on Clinical Gov database the 8 October 2013

## Background

There were approximately 87 million people aged 65 years old in 2010 in the European Union (17.4% of the total population) compared with just 59.3 million people (12.8%) in 1985 [1]. This phenomenon of an aging population requires a more efficient resources allocation in health care; the demand of health treatments coming from an aging population can be fulfilled through the implementation of new procedures, mostly based on behavioral theories [2]. For instance, the biological aging process is associated with structural and functional deterioration in most physiological systems, including the neuromuscular and cardiovascular systems [3-10]. These deteriorations can affect the ability of older adults to cope with and perform everyday activities. Consequently, there has been a tendency - amongst both the medical community and general public - to view older people as vulnerable, unproductive, and non-contributing members of society. However, in recent years, attitudes have begun to change and emerging research insights demonstrate that an active and engaged lifestyle in older adults contributes not only towards successful aging, but to a healthy economy and society more generally [11]. Indeed, many older adults with active participation in social and leisure activities report good levels of psychological wellbeing [4]. These behavioral approaches to health care are increasingly applied to different treatments.

The activity theory of aging suggests that wellbeing in older adults is promoted by (a) higher levels of participation in social and leisure activities, and (b) role replacement when roles must be relinquished [12]. In addition to the benefits of remaining psychologically stimulated, social and leisure participation may also maintain or promote wellbeing in older adults due to increased physical activity. For example, research demonstrates that the activation of bodily systems promotes a greater range of motion and muscle tone, and improves digestive system functioning and cardiovascular health [11]. More specifically, endurance training is purported to be effective for decreasing fat mass [13], resting heart rate [14] and blood pressure [15], and resistance training can increase basal metabolism [16], bone mineral density (BMD) [17], muscle strength and power [18], and muscle and connective tissue cross-sectional area [19].

A recent review [11] has suggested that successful aging training programs can be distinguished by both the content (that is, the mental and physical demand and/or behavioral aspects) and the social context of the activities. Social activity affects wellbeing by reducing the risks of social isolation and facilitating (a) emotional intimacy, (b) socio-emotional support, (c) reinforcement of self-identity and social roles, and (d) a sense of being valued. Furthermore, productive activity may influence health and wellbeing in older adults through satisfaction with outcomes, economic gains, mental stimulation, comforting personal routines, sense of purpose, and increased self-efficacy and/or self-esteem [20].

As already indicated, psychological wellbeing is a key determinant of quality of life in older people. According to the *Broaden and Build Theory of Positive Emotions*[21], negative emotions serve to narrow focus and attention, whereas positive emotions serve to broaden thoughts and behaviors. Thus, by broadening their thoughts and actions, older-aged adults are better able to cultivate positive emotions and build important coping resources including psychological, intellectual, and physical aptitude. Indeed, there is a strong correlation between quality of life and attitudes towards aging in older adults [22]. Of particular interest in this regard, are gender differences in terms of physical activity engagement. For example, due to factors such as menopausal transition (MT), there is evidence to suggest that older women are less likely to engage in physical activity than older men [23]. This in turn can compound stress levels and increase the risk of depression [24].

Several training methods such as aerobic training, strength training, multicomponent exercise training and whole body vibration (WBV) may improve health outcomes in older-aged women [25]. WBV utilizes high frequency mechanical stimuli (generated by a vibrating platform) that are transmitted through the body where they load the bone and stimulate sensory receptors. Multicomponent exercise training comprises strength training and various balance improving exercises. Significant health improvements are associated with multicomponent exercise training programs in older-adult samples, including the prevention of bone fractures and osteoporosis [22,25,26]. Likewise, WBV is associated with improvements in strength, power, and balance in body composition [27-29] - including in obese women [30]. Findings also demonstrate that occupational exposure to WBV is associated with favorable alterations in mood state that are directly proportional to exposure time [31]. Despite these promising findings, very few studies have focused on the link between these exercise training programs and psychological outcomes (for example, quality of life, psychological wellbeing, happiness, and so on) in older women. Accordingly, the aim of this study is to conduct a randomized controlled trial that assesses these relationships in order to inform the structure and development of exercise training programs for older women.

## Methods/Design

### Hypotheses and design

Starting from current literature, we hypothesize that specific physical activity, WBV, may promote psychological wellbeing and quality of life in female aged subjects, if compared with Multicomponent Training program and normal physical activity. Therefore, we assume an improvement in proactive attitude, quality of life, wellbeing and happiness of WBV training group when compared to and Multicomponent Training and control group.

The comparison among WBV group, Multicomponent Training group and control group will be assessed in a three-arm randomized controlled clinical trial (Figure 1).

**Figure 1 F1:**
[figure not shown]
Study design.

All eligible participants will be approached by trained clinical psychologists and will be screened for psychological aspects concerning the general wellbeing, the proactive attitude and the health status. Participants will, moreover, be informed of the protocol and procedures prior to their involvement and written consent to participate will be obtained. Informed consent will be sought for: (a) using anonymous data from the questionnaires for reports and scientific publications; and (b) for informing the general practitioner (GP) about the study results.

### Setting

The study will be conducted in collaboration with the University of Bergamo (Italy) and the Catholic University of San Antonio of Murcia (Spain). The Psychological scale administrations and training intervention will be conducted at the biomechanics lab in the UCAM Research Center for High Performance Sports. Different settings will be utilized due to the different nature of the exercises. The WBV training will in fact be carried out at the lab and the Multicomponent Training in a garden close to the research center.

### Subjects

A non-probability sampling intentional/convenience will be used for sample selection. Participants with the following eligibility criteria will be included in the present study: women; age ranged between 55 to 75 years old. Exclusion criteria included: male sex; age lower than 55 years old; present levels of bone mineral density (BMD) lower than 70 g/cm^2^; being treated for a disease that can affect bone structure or neuromuscular system; have orthopedic prosthetic implants in the lower limbs and/or spine; have herniated discs; suffer ocular diseases that affect the retina; suffer severe cardiovascular diseases; have a pacemaker, or osteosynthesis material *in situ*; severe mental illness (active psychosis/suicide risk/severe dementia); linguistic limitations (such as stuttering/untreated audio impairment); a significant functional problem (such as unconsciousness/connection to respiration device/confinement to a wheelchair or bed/severe walking disability/need of help with basic daily activities), major depression, anxiety according to *Diagnostic and Statistical Manual of Mental disorders, version 4* (DSM-IV) criteria.

### Randomization

Randomization will be performed by statistical experts of the team study using a computerized random number generator at (http://www.randomizer.org/). To obtain equal numbers in both conditions, a block randomization design is chosen. After the completion of the inclusion procedure, the clinical psychologist will obtain the file containing the condition to which the patient is allocated.

### Interventions

The interventions protocol will consist of six months of training for both groups of vibratory platform and Multicomponent Training. Both groups, WBV and Multicomponent Training, will follow three training sessions per week, with a recovery time between sessions ranging from 24 to 72 hours.

### WBV training

After the warm-up consisting in eight minutes of static cycling, active stretching and joint mobility, participants will perform the WBV training. The vibration stimulus will consist of uniform vertical oscillations Power Plate® Next Generation (Power Plate North America, Northbrook, IL, USA). Subjects will stand on the platform holding quarter squat positions with the feet shoulder-width apart. Then, they will perform ankle extensions with the following work sequence (establishing a rhythm of 100 bpm: 1 bpm for the concentric phase; and 5 bpm for the eccentric phase). After the familiarization 2-weeks, subjects will train 3 days per week for 6 months (72 sessions) using a vibrating training program that will begin with 5 sets and a frequency of 35 Hz per session and increasing by 11 sets and 40 Hz frequency for the last month, maintaining a series of parameters: vibration amplitude (4 mm) working time (60 seconds) and recovery time (60 seconds).

### Multicomponent Training

In the same way, and after the warm-up consisting in eight minutes of static cycling, active stretching and joint mobility, participants will perform the Multicomponent Training. This training will combine vertical jumps and high-intensity walking. During the first month, small reactive vertical jumps (without knee and ankle flexion) will be performed. After the first month, subjects will perform drop jumps progressively starting at a height of 5 cm and finishing at 25 cm at the end of the program (increases of 5 cm each month). Additionally, the sets will be increased from 4×10 jumps to 6×10 each week, finishing the last week with 4×10. In this sense, the drop jumps will be the same each month but the total load (imposed by height) will increase progressively. Regarding the aerobic exercise, the load will increase progressively along the six months. The intensity will range between 50 to 75% of reserve heart rate; the volume will range between 30 to 60 minutes.

